## 2. Materials and Methods

### 2.1. Study Objectives and Design

The study objective is to evaluate the feasibility and acceptability of the trial protocol and the exploratory benefit of Peers EXCEL compared to HLWD using a pilot randomized controlled intervention mixed methods trial, among African Americans with uncontrolled diabetes. We will randomize participants to receive either Peers EXCEL or HLWD only. All individuals who agree to participate will be assigned a number and allocated to either the Peers EXCEL or HLWD group using computer-generated random numbers. The randomization process is illustrated in Figure 1. The study duration will be December 2022 until September 2023.

Our study aims are to:(1)Evaluate if the intervention and protocol are feasible and acceptable. We will investigate if Peers EXCEL would be feasible to implement and be acceptable to African Americans with uncontrolled type 2 diabetes. Qualitative and quantitative data from multiple sources will be integrated to allow for meta-inferences about the feasibility of conducting a future large-scale effectiveness RCT.(2)Pilot test Peers EXCEL to examine its effect in improving A1C and medication adherence. We hypothesize a signal of change in mean hemoglobin A1c that is clinically meaningful (≥0.6 reduction) for participants randomized to Peers EXCEL compared to participants randomized to HLWD at baseline, 2 months, and 6 months. We expect to see an improvement in medication adherence, assessed via self-report in the Peers EXCEL participants compared to the HLWD participants at 6 months.

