#### 2.5.2. Screening

Participants Screening: We will implement successful strategies used in our preliminary work and prior studies [22,23,43]. Eligible participants will complete a two-step screening process: (1) preliminary phone screening—A program assistant will ask if the individual meets the eligibility criteria including having a recent A1C value that showed ≥7.5%, and then (2) point-of-care A1C test to confirm that their A1C is ≥7.5%.Ambassador Screening for the Peers EXCEL arm: Based on our prior successful pilot study [22,23,43], after a ambassador candidate is known, a program assistant will complete a brief preliminary ambassador candidate screening form, ask the individual if they have had recent A1C values that are ≤7.5% and then, a point of care test to evaluate their A1C will be scheduled for verification. After these screenings are completed, the PI, program assistant, and research team members will meet with the candidate to explore other important characteristics, including their communication skills, and mentoring experiences. These characteristics will help inform the research team in the matching of an ambassador to a participant.

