### 2.7. Data Analysis

Quantitative. Paired *t*-tests (or a non-parametric corresponding test such as Wilcoxon rank sum test) will examine pre- vs. post-intervention changes in participant’s A1C, medication adherence, and other psychosocial outcomes across groups to examine a signal of change. We will use descriptive statistics to calculate ambassadors’ feasibility measures, HLWD and Peers EXCEL participants, including ambassador recruitment, ambassador attrition, and extent of ambassador participation in sessions related to their training and intervention. We will consider the recruitment approach as feasible if: there is recruitment of all ambassadors and participants as planned, attrition for both ambassadors and participants is less than or equal to 10%, and the rate for ambassador and participant participation is equal to or higher than 80%.Qualitative. Interviews and focus groups will be audio-recorded and transcribed. Research assistants will code transcripts inductively using NVivo v 12 and conduct qualitative content analysis [56]. Qualitative content analysis will be used to organize the themes. All transcribed transcripts will be read initially for data immersion, taking time to read all the data line by line. Then, the codes and themes will be developed and organized with a conceptualization of how the themes are all lined together in the data. We will compare all themes exploring if there are similarities, interconnections, and/or differences across all themes. We will continue all data analysis until we get to theoretical and there are no more new dimensions in the data [57,58,59]. We will establish rigor of the data and explore the trustworthiness of the data analysis process using Lincoln and Guba (1985) four general criteria [60]. These are credibility, transferability, dependability, and confirmability. For credibility, two research assistants will code the transcripts independently—investigator triangulation (i.e., multiple coders involved in the data analysis), discuss similarities and divergences, and reach agreement by consensus before the final data interpretation. We will member check with participants interested in being part of the process to confirm if our interpretation is salient/credible—to check for resonance with participant experiences. Confirmability, objectivity/potential congruence between researchers. To ensure our findings are based on our participants’ responses and not any personal motivations or personal bias from our research team, after coding, all similarities and divergences will be discussed. Agreement will be reached on codes before results interpretation. Transferability, the scope to which results are applicable to other contexts. We will purposively sample individuals with varied intervention experiences and use detailed descriptions to show how the research study’s findings may be applicable in other contexts, circumstances, and situations. Dependability—the ability to achieve consistent findings if the study is done as described. We will create and report a detailed audit trail of our process throughout the analysis process. Documents and field notes data will also be analyzed using content analysis.Mixed. After analyzing the quantitative and qualitative data separately, the mean score differences, statistical effect sizes, and themes will be compared in the context of the feasibility, acceptability, and primary and secondary outcomes. The results from both phases will be interpreted together in a joint display to aid a meta-inference of the merged results.

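### The planned paired pre-post tests of A1C and adherence do not assess the Peers EXCEL versus HLWD contrast stated in both clinical hypotheses

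*Protocol article*

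**What the plan says.** Section 2.1 sets up a randomised comparison: "We will randomize participants to receive either Peers EXCEL or HLWD only". Its second aim hypothesises an effect on A1C, described as "clinically meaningful (≥0.6 reduction) for participants randomized to Peers EXCEL compared to participants randomized to HLWD at baseline, 2 months, and 6 months". The adherence hypothesis has the same form: improvement "assessed via self-report in the Peers EXCEL participants compared to the HLWD participants at 6 months". Section 3 repeats both.

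Section 2.7 holds the only quantitative analysis text. Paired t-tests "will examine pre- vs. post-intervention changes in participant’s A1C, medication adherence, and other psychosocial outcomes across groups to examine a signal of change". The alternative is given in brackets: "or a non-parametric corresponding test such as Wilcoxon rank sum test". Later in the same section, under the mixed analysis, "the mean score differences, statistical effect sizes, and themes will be compared in the context of the feasibility, acceptability, and primary and secondary outcomes".

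Two design facts bear on this. Section 2.5.4 gives the intervention arm the HLWD classes plus extra content and peer support, so both arms receive HLWD, and the Introduction says that HLWD improves health outcomes. Sections 2.4 and 2.5.2 select participants on the outcome variables: self-reported nonadherence, and a "point-of-care A1C test to confirm that their A1C is ≥7.5" percent.

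**The concern.** The hypotheses compare two randomised arms. A paired t-test compares each participant with their own baseline. Run separately by arm, it yields two statements about change over time and none about the difference between them. Run on all 24 participants together, it ignores arm.

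Within-arm change is a poor stand-in for the contrast in this design. The control is an active programme and entry is conditional on poor values of the outcomes, so A1C may fall in both arms even if the added Peers EXCEL content does nothing. A pre-post fall could then be reported as a signal for Peers EXCEL. The earlier pilot already supplied a pre-post figure (−0.7 at 6 months). The comparison with a control is what this trial adds.

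**Working it through.** **No plan figure to reproduce.** The article gives no alpha, SD or sample-size calculation. The arithmetic below is an illustration.

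**The texts side by side**

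| Place | Contrast |
|---|---|
| 2.1 and 3, A1C | Peers EXCEL versus HLWD, reduction of at least 0.6 |
| 2.1 and 3, adherence | Peers EXCEL versus HLWD at 6 months |
| 2.7, named test | Post versus pre, same participant (paired t) |
| 2.7, alternative | Rank sum: two independent samples. The counterpart of a paired t-test is the signed-rank test |
| 2.7, mixed analysis | Mean differences and effect sizes, contrast not defined |

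No line of 2.7 clearly names a between-arm difference, a baseline-adjusted model or an arm-by-time term.

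**Inputs.** From the article: 12 per arm (2.4); a fall of 0.7 in the earlier pilot (Introduction); target 0.6 (2.1). Assumed: the same 0.7 fall in both arms, so no true difference; SD of individual change 1.0 to 1.5; two-sided alpha 0.05; normal changes.

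**Within-arm paired test.** Noncentrality = 0.7 / (SD/√12).
- SD 1.0: 0.7/0.289 = 2.42, rejection 60%.
- SD 1.5: 0.7/0.433 = 1.62, rejection 31%.

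**Pooled paired test.** Noncentrality = 0.7 / (SD/√24).
- SD 1.0: 0.7/0.204 = 3.43, rejection 91%.
- SD 1.5: 0.7/0.306 = 2.29, rejection 59%.

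**Two-sample t-test on change.** Rejection is about 5% at either SD, as it should be when the arms do not differ.

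The within-arm figures come from the noncentral t and agree with a simulation of 40,000 trials. The pooled and two-sample figures come from that simulation. At SD 2.0 the within-arm and pooled figures are 20% and 38%. With 11 per arm (attrition near the 10% criterion) they are 55% and 88% at SD 1.0, and 29% and 55% at SD 1.5.

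**What the between-arm estimate would deliver.** 95% CI half-width = t(0.975; 22) × SD × √(2/12) = 2.074 × 0.408 × SD.
- SD 1.0: 0.85 points.
- SD 1.5: 1.27 points.

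Power for a true 0.6 difference is 29% at SD 1.0 and 15-16% at SD 1.5. For 80% power the normal approximation, 2 × (1.960 + 0.842)² × SD² / 0.6², gives 44 and 99 per arm.

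**Baseline adjustment.** The ANCOVA variance relative to change scores is (1 − r²) / [2(1 − r)] = (1 + r)/2, where r is the baseline to 6-month correlation. At an assumed r of 0.5 to 0.7 this is 0.75 to 0.85, a saving of 15-25% in variance.

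**The case against.** The best defence is that 2.7 does not exclude a between-arm comparison. The phrase *across groups* could mean that changes are compared between the arms. The rank sum test would suit that reading, and the effect sizes in the mixed analysis could be between-arm. This stands in part: the section is ambiguous, and it would be wrong to say that paired tests are the only method it mentions. It does not rescue the sentence. The lead test is paired, and the rank sum test is offered only as its counterpart.

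The second defence is that this is a feasibility pilot. Benefit is exploratory, the feasibility criteria in 2.7 do not use the A1C test, and the corrected contrast would be imprecise. That stands and sets the severity. It does not make a pre-post test an answer to a between-arm question.

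Three stronger readings are tempting, and the documents do not support them.
- A reader might infer that the trial would yield no usable between-arm estimate or SD. If the tests are run by arm, each gives a mean and SD of change, and the contrast follows by subtraction.
- A reader might infer a false-signal rate from the pattern of significance in Peers EXCEL but not in HLWD. The article states no such decision rule. Its A1C signal is a size, and it called the earlier −0.7 clinically meaningful without statistical significance.
- A reader might put a figure on regression to the mean. That needs the screening test to serve as baseline, but 2.5.3 and 2.5.4 list A1C collection at Week 0 and do not say whether it is the same measurement.

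Also, an improvement in adherence from HLWD alone is less certain than one in A1C, since the Introduction says HLWD has only brief content on medicine use.

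**Conclusion.** The point holds as a mismatch between the hypotheses and the stated analysis. Followed as written, 2.7 does not assess the Peers EXCEL versus HLWD contrast, and its non-parametric alternative does not match the test it replaces. This conclusion needs no numerical assumption.

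The sizes do. Rejection in 31-60% of trials within an arm, or 59-91% pooled, with no arm difference rests on an equal 0.7 fall in both arms, SD of change 1.0-1.5 and alpha 0.05. The article gives no A1C change for HLWD and no SD. The figures show that a pre-post result can look positive for reasons unrelated to Peers EXCEL; they do not predict this trial's result.

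Severity: should-fix. The clinical aim is exploratory and the feasibility conclusions are not affected.

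**What to change.** Replace the paired-test sentence in 2.7 with the following:
- The main clinical result is the between-arm difference (Peers EXCEL minus HLWD) in 6-month A1C, adjusted for baseline A1C by ANCOVA, with a 95% CI. The adherence score is treated in the same way. A between-arm comparison of change from baseline is also valid and would resolve the mismatch.
- The 2-month differences are secondary.
- The result is presented as an estimate and not as a confirmatory test.
- Within-arm changes are descriptive.
- If a non-parametric test is kept, the rank sum test is applied to changes between arms.
- The mean differences and effect sizes in the mixed analysis are stated to be between arms.
- The A1C measurement that counts as baseline is named.

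The cost is wording only, since Table 4 already schedules A1C and adherence at all three visits. The downside should be stated openly: the interval will be wide, with a half-width of about 0.85 to 1.27 points on change scores at SD 1.0-1.5, which exceeds the 0.6 target.

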## Abstract

Background: Due to diabetes disparities commonly seen among African Americans, it is important to address psychosocial and sociocultural barriers to medication adherence among African Americans with diabetes. Building on our prior work testing a culturally adapted peer supported diabetes self-management intervention for African Americans, this study will conduct a pilot randomized controlled feasibility trial that compares the culturally adapted intervention with a standard diabetes self-management program. Methods: Using an intervention mixed-methods design, the six-month trial will be conducted at two sites. Twenty-four African Americans with uncontrolled type 2 diabetes will be randomized to the intervention or control arm. Feasibility and acceptability outcomes in four domains (recruitment, intervention acceptability, intervention adherence, retention) will be collected. Primary clinical outcome (A1C), secondary outcome (medication adherence) and patient-specific psychosocial measures will be collected at baseline, 2 months, and 6 months. Document review, interview and focus groups will be used to gather qualitative data on feasibility and acceptability. Results: Expected results are that the trial protocol will be feasible to implement and acceptable for participants, and there will be a signal of clinically meaningful reduction in A1C and improvements in medication adherence. Conclusions: The results of this trial will inform a future powered large-scale randomized controlled trial testing the effectiveness of the culturally tailored intervention.

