Peers EXCEL provides an adapted diabetes self-management program for African Americans which includes group education sessions and one on one peer support. Group education includes the addition of new sessions that address misperceptions about diabetes and medicines influenced by racial discrimination/mistrust of providers, building self-efficacy, and provider communication. The additional one-on-one peer support occurs through race-congruent phone follow-up from other African Americans called Ambassadors. *Ambassadors* are African Americans with diabetes who are adherent to their medicines paired with African Americans with diabetes who are nonadherent (*Buddies*). Ambassadors’ interactions with their buddies focuses on addressing medicine and diabetes misperceptions, sharing experiences managing diabetes and medicines, and supporting self-efficacy and self-advocacy with their healthcare providers [31]. In the pilot trial of Peers EXCEL that examined feasibility and acceptability, we found the rates of recruitment were 80% for buddies and 100% for ambassadors. The rate at which the primary outcomes, medication adherence and A1C were retained was 75%. Participants mean completion rate was 13.4/17 of group sessions and phone calls with their ambassadors. About 84% of intervention phone calls were completed between the ambassadors and their buddies. We found no statistically significant differences in mean A1C and medication adherence. However, we found a clinically meaningful reduction (−0.7) in mean A1C at the inference point, 6-month follow up compared to the baseline. Based on the qualitative themes, participants reported the program to be culturally appropriate and acceptable with a perception of improved communication with their provider. They also reported that they learned strategies to assist with goal setting, and developed the confidence and motivation they needed for self-management [23].

Given these results, our next step is to conduct a pilot randomized controlled trial (RCT) of Peers EXCEL compared to HLWD to examine the feasibility and acceptability of the intervention and protocol and explore the benefits of the intervention in African Americans with uncontrolled diabetes using mixed methods.

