### 2.6. Data Collection

Quantitative data will be collected using in-person surveys at baseline, 2 months, and 6 months. Qualitative interviews and focus groups will be conducted with all study participants, HLWD facilitators, and the ambassadors to understand their experiences with the intervention and their feedback on the program. These interviews will be conducted at 2 and 6 months. Field notes and documents from program assistants will be reviewed for data abstraction.

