
## 3. Expected Results

It is expected that the intervention trial protocol will be feasible to implement and be acceptable to African Americans with type 2 diabetes. Finally, we expect that participants who complete the Peers EXCEL intervention will have a signal of change in mean A1C that is clinically meaningful (≥0.6 reduction) compared to participants randomized to HLWD at baseline, 2 months, and 6 months. The primary outcome is to see a reduction in A1C, while the secondary outcome will be to determine if there is an improvement in medication adherence, assessed via self-report in the Peers EXCEL participants compared to the HLWD participants at 6 months.

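### The paired pre/post tests in 2.7 drop anyone without a 6-month A1C even when a 2-month value exists; selective loss can then shift a within-arm change by about 0.06 to 0.29 points under assumed inputs

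*Protocol article*

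**What the plan says.** Section 2.7 (Data Analysis) names paired t-tests, or a non-parametric counterpart, which "will examine pre- vs. post-intervention changes in" each participant's outcomes: "A1C, medication adherence, and other psychosocial outcomes across groups to examine a signal of change". It does not say whether the post value is the 2-month or the 6-month one.

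Section 2.6 schedules three measurements: "Quantitative data will be collected using in-person surveys at baseline, 2 months, and 6 months". Table 4 lists A1C at all three.

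The target is a contrast between arms. Section 2.1 expects a change that is "clinically meaningful (≥0.6 reduction) for participants randomized to Peers EXCEL compared to participants randomized to HLWD". Section 3 words the same expectation for a selected group: "we expect that participants who complete the Peers EXCEL intervention will have a signal of change in mean A1C", set against participants randomised to HLWD.

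Two figures bear on loss. For the team's earlier pilot, section 1 reports: "The rate at which the primary outcomes, medication adherence and A1C were retained was 75" (per cent). For this trial, section 2.7 calls recruitment feasible only if "attrition for both ambassadors and participants is less than or equal to 10" (per cent).

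**The concern.** A paired test needs both values. A participant who attends at baseline and 2 months and then leaves is absent from the 6-month comparison, although the 2-month A1C says a good deal about where that person was heading. Running separate tests at 2 and 6 months does not change this, because each test still uses two visits.

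If those who leave are mainly those who are not improving, the remaining pairs show a fall in A1C with no treatment effect. The arms also differ in burden. Peers EXCEL has eight group sessions plus ambassador calls (2.5.4), and HLWD has six sessions (2.5.3). Unequal loss is therefore possible, though nothing in the article shows that it will occur. The wording of section 3 points the same way, since it sets completers of one arm against everyone randomised to the other.

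The A1C result is meant to inform a later powered trial, so a systematic shift in it would carry into that trial's planning.

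**Working it through.** **Inputs from the article.** "Twenty-four African Americans with uncontrolled type 2 diabetes will be randomized to the intervention or control arm", which is 12 per arm. Earlier pilot loss is 100% - 75% = 25%, or 3 of 12. This trial's attrition limit is 10%, or about 1 of 12. The target is 0.6 A1C points. The article gives no SD, correlation, power or bias figure, so there is no stated figure to reproduce.

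**Assumed inputs.** A1C SD 1.5 at each visit; correlations 0.7 (0 to 2 months), 0.6 (0 to 6 months) and 0.8 (2 to 6 months); no true effect; loss at 6 months logistic in the 2-month change, with the odds of loss multiplied by about 1.6, 2.7 or 4.5 per point of worse change (log-odds slopes 0.5, 1.0 and 1.5).

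**Step 1: identity.** Let d be the share lost and gap the mean A1C change of those lost minus that of completers. Then

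completers' mean - full mean = -d × gap.

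- d = 0.25: gap 0.5 gives 0.125 (21% of 0.6); gap 1.0 gives 0.25 (42%); gap 1.2 gives 0.30 (50%).
- d = 0.10: gap 1.2 gives 0.12 (20%); a shift of 0.30 would need a gap of 0.30/0.10 = 3.0 points.

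**Step 2: simulation.** The intercept of the loss model was set so that average loss is 25% or 10% in every row.

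| Odds of loss per point | Shift at 25% loss | Share of 0.6 | Shift at 10% loss | Share of 0.6 |
|---|---|---|---|---|
| 1.6 | -0.13 | 22% | -0.06 | 9% |
| 2.7 | -0.23 | 38% | -0.10 | 17% |
| 4.5 | -0.29 | 48% | -0.13 | 22% |

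(The -0.06 is -0.055 before rounding.) The calibration matters. With the intercept fixed at odds 0.25/0.75, loss rises to 26%, 29% and 33% and the shifts become -0.14, -0.27 and -0.37, which no longer describe 25% loss. Step 1 agrees with the bottom row: 0.29/0.25 is a gap of about 1.2 points.

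**Step 3: between arms.** Bias of the contrast = shift in Peers EXCEL - shift in HLWD. Equal selective loss in both arms gives zero. The table's values carry over in full only if selective loss is confined to Peers EXCEL.

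**Step 4: sampling error.** The SD of the 6-month change is 1.5 × √(2 × (1 - 0.6)) = 1.34. The SE of the arm difference is 1.34 × √(2/12) = 0.55 with 12 per arm, or 1.34 × √(2/9) = 0.63 with 9 per arm. The largest shift, 0.29, is about half of that.

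**Step 5: what the third visit recovers.** When loss depends on the observed 2-month change, an estimate that regresses the 6-month value on baseline and 2-month values has bias of about 0.00. When loss depends on the 6-month change itself (25% loss, same slopes), the complete-pair shifts are -0.21, -0.35 and -0.43, and the all-visit estimate still shows -0.10, -0.17 and -0.23, about half. This regression estimator stands in for the mixed model, which was not itself fitted.

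**The case against.** A reader might infer that drop-out alone will create about half of the 0.6 signal. The documents do not support that. The 48% is the steepest of three assumed scenarios. It needs drop-outs to do about 1.2 points worse than completers, and none of the selection inputs is in the article. The 25% belongs to an earlier pilot. This trial sets a 10% limit and plans weekly check-in calls to every participant (3.1). The 0.6 is a between-arm target, and the shift is a within-arm one that cancels if both arms lose people alike. All of this stands, and it limits the size of the point.

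A reader might also infer that the plan ignores one of the visits altogether. Section 2.7 does not define the post visit, so tests at both 2 and 6 months fit the text. What stands is only that no single paired test uses the 2-month value to inform the 6-month result.

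Handling of missing data is commonly left to the SAP, which is not shown, so its absence is no finding. The point is made against the test that the article names and against the completer wording in section 3.

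Finally, this is a 24-person feasibility pilot whose sampling error exceeds the bias. That is true, and it makes the matter modest. It does not justify discarding A1C values that are already being collected.

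**Conclusion.** The point holds as a modest one. The named paired tests use complete pairs only and so waste the 2-month A1C of anyone lost before 6 months. Under the assumed SD, correlations and loss model, the within-arm change moves by -0.13 to -0.29 at 25% loss and by -0.06 to -0.13 at 10% loss, with no true effect. How much reaches the arm contrast depends on how far selective loss differs between arms, which the article does not allow one to judge. Using all three visits removes the bias only if loss depends on observed values; otherwise about half remains. Confidence in the mechanism is high. The size is conditional on the assumptions.

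**What to change.** In 2.7, estimate the 6-month A1C arm contrast from one linear mixed model on the baseline, 2-month and 6-month values, with visit, arm and arm-by-visit terms and a small-sample degrees-of-freedom correction. Include every randomised participant with any value, and keep the paired changes as description.

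Add two items: a table by arm of the baseline and 2-month A1C of those without a 6-month value, and a simple sensitivity range in which missing 6-month values are set worse than the model predicts, by amounts that may differ between arms.

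In section 3, word the expected A1C result for participants randomised to Peers EXCEL instead of those completing it.

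The cost is analysis and reporting text only. No visit, measurement or participant is added, and the model's assumption about loss is weaker than that of the complete-pair test.
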